## 6.11 Adverse Events and Social Harms

All adverse events or unanticipated problems associated with the procedures of any component of this study will be reported within the time frames required by the Institutional Review Boards at UNC and MUHAS. Appropriate action will be taken to address any adverse events or incidents. Reports will be made using standard forms available from the relevant IRBs for adverse events or unanticipated problems associated with the study procedures or participating individuals.

Participants will be provided with information on how to contact the local research staff to report such events as breaches of confidentiality, HIV-related disruption of families, acts of discrimination, and physical harm. We will ask participants to return to the research site or otherwise contact research staff in order to make such reports as well as receive referrals to mitigate potential harm.

If staff members experience occupational exposure to HIV, the incident will be reported and a protocol will be followed to minimize their risk of being infected with HIV that includes the provision of post-exposure prophylaxis with antiretroviral drugs when indicated. All staff at risk for occupational exposure to HIV will be trained on universal precautions and on the post-exposure prophylaxis protocol. All staff performing HIV tests will require training and certification on performing the test and on quality assurance.

Adverse events reporting in this trial has been considered in the context of several important characteristics of the study. First, this is a minimal-risk study as defined in federal regulations—“the probability and magnitude of harm or discomfort anticipated in the research are not greater in and of themselves than those ordinarily encountered in daily life or during the performance of routine physical or psychological examinations or tests.” Second, all participants in this study are de-identified using Personal Identification Numbers. Participant data will not be linked to names. We have chosen this approach to maximally protect the confidentiality of those volunteering for HIV testing and counseling. Third, although no clear guidance is currently provided in regulation for adverse events reporting in behavioral studies such as this one, as opposed to clinical trials of drugs or devices, we are taking the steps outlined above within the context of our study.

All study staff/volunteers having potential contact with study participants or data will receive human subjects training.

## 6.12 Security and Confidentiality

Strict security procedures will be followed to ensure confidentiality and security of data for all components of the study. Study documentation will be kept in locked files in study site offices. To ensure confidentiality, questionnaire data will be encrypted and saved on password-protected secure computers. Personal identifiers will not be stored in the data set and all computers will be protected by antivirus software.

# 7. EVALUATION OF OUTCOMES

## 7.1 Overview

This is a cluster-randomized controlled trial to measure the efficacy of a combined microfinance and health promotion intervention. A total of 60 camps will be randomized to receive the intervention or the control. The primary endpoint will be STI prevalence measured with biological assessments at baseline and at 30 months, and gender based violence perpetration and HIV-risky behaviors measured at baseline, 12 and 30 months with behavioral assessments.

## 7.2 Primary Endpoint - STI Prevalence

For the proposed study, men will provide a first-catch urine specimen for NG, CT and TV testing by polymerase chain reaction (PCR). The introduction of nucleic acid amplification tests (NAATs), including PCR for the detection of sexually transmitted pathogens, has provided critical new tools for diagnosis of infections with Neisseria gonorrhea (NG), Chlamydia trachomatis (CT) and Trichomonas vaginalis (TV). NAATs are substantially more sensitive than culture or antigen detection assays, and specific detection of multiple STI pathogens in men is possible using traditional urethral specimens and, importantly, in noninvasive urine specimens. Study participants who are identified with NG, CT, or TV will be offered treatment according to the standard of care in Tanzania: NG (Ceftriaxone), CT (Doxycycline), TV (Metronidazole).

Blood will be obtained for serologic tests to detect antibodies indicating infection with HIV. We will use Immnochromatographic tests (ICT), which are Alare Determine ^TM^ HIV 1/2 as Test 1 and Unigold ^TM^ HIV as Test 2. An Immuno-Chromatographic test (ICT) is used for the qualitative detection of antibodies to the human immunodeficiency virus (HIV) type 1 and 2 in blood. The blood sample flows along the strip and if HIV antibodies are present, the antigen/antibody complex binds with a conjugate forming red band. If antibodies to HIV are absent no red band is formed. To ensure assay validity, a procedural control band is incorporated into assay device.

### 7.2.1 Training, Quality Assurance, and Project Expertise for Lab

QA will be performed on each new lot of rapid test kits that arrives at sites by running the controls and testing one positive and one negative sample of known sera. To ensure the validity of each HIV test, a procedural control line is incorporated into the strip or device and is labeled “Control”. The control line must appear in all tests, whether positive or negative. Internal controls will be used in NG, CT, and TV tests to ensure validity.

### 7.2.2 Specimen Collection

Good Clinical Practices will be followed by all nurses collecting biological specimens to ensure the safety of participants and self. For each participant providing blood nurses will put on new gloves and select a new syringe and needle. After sanitizing the area of needle insertion, the nurse will draw at least 1 mL blood in a 2mL syringe and transfer to a 4 mL container. For urine specimen collection participants will be instructed to fill a 30 mL container up to a pre-marked 20 mL line with first catch urine. Both containers will be labeled with biological ID numbers and stored in a cooler at 18-25 degrees C until the end of the day.

### 7.2.3 Specimen Handling, Storage, and Shipping

Specimen (both urine and blood) will be transported from the field to MUHAS lab every day. Nurses will make sure each collected specimen has been stored in cooler boxes and ready for transportation. The Lab Coordinator will count and transport all collected specimen, and ensure transport at a temperature between 18 -25 degrees C to MUHAS. Blood samples will be processed at the MUHAS lab.

Urine sample will be and frozen to -20 C upon arrival at the MUHAS lab. At the end of each week the frozen specimens will be transported to the NIMR Mwanza laboratory for processing and further storage. There will be a tracking form for both urine and blood specimen.

Extra specimen will be stored in a -20 C freezer in the MUHAS lab should a re-test of any specimen be necessary.

## 7.3 Primary Endpoint - Gender-based Violence Perpetration

We will measure violence using the WHO violence against women instrument.([Garcia-Moreno, Jansen, Ellsberg, Heise, & Watts, 2006](#_ENREF_28)) This instrument is built on methodological work and research on violence by partners using the Conflict Tactics Scale. We have used these questions previously to measure young men’s perpetration of violence in Tanzania.([Maman, Yamanis, Kouyoumdjian, Watt, & Mbwambo, 2010](#_ENREF_51)) Psychometric analyses of these items reveal that they load on two factors, physical and sexual violence, and both factors are internally consistent. We will also include questions on emotional abuse from this scale. The physical violence items include instances of slapping, pushing, hitting, kicking, choking and threatening with a weapon. Sexual violence items include physically forcing a partner to have sexual intercourse or physically forcing a partner to do something sexual that is degrading or humiliating. Emotional abuse questions include instances of insulting, belittling in front of others, intimidating, and threatening to hurt someone the partner cared about. Men will be asked if they have ever perpetrated these instances with their current or any other partner. For questions answered ‘yes’, men will be asked how many times they have perpetrated these instances in the last 12 months as well as before the last 12 months. These questions will be followed up with the same questions but asked as the men as victim of these instances rather than perpetrator. We also included a question on physical violence and one on sexual abuse before age 12.

## 7.4 Secondary Outcomes - Behavioral Outcomes

All secondary outcomes except for microfinance outcomes will be measured at baseline, 12 months and 30 months. Microfinance outcomes will be measured at 12 and 30 months only.

### 7.4.1 HIV risk behaviors

**Consistent condom use with recent partners**

For each of their three most recent sexual partners, men will report how many times they engaged in sex (oral, anal, vaginal) with these partners during the past month, and for how many of these times they used a condom.

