**Sexual Network**

We will assess the sexual behaviors of participants with up to three partners with whom they have had the longest sexual relationship in the last year. Participants will first be asked to give the nickname of these partners, then will be asked about relationship longevity, confidence in condom negotiation, condom use, alcohol use before sex, concurrency, confidence in discussing HIV, HIV testing, and physical abuse.

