***Interviewer:***

→ Now I would like to ask some more personal questions about you and your relationships. Please remember that your answers will be confidential.

| **No.** | **Questions and Filters** | **Coding Categories** | **Codes** | **Skip to:** | **VARIABLE** |
| --- | --- | --- | --- | --- | --- |
| Q1401 | Have you ever had sex?  • Vaginal sex is when a man puts his penis in the vagina of a woman; [some people call this [Swahili term].  • Anal sex is when a man puts his penis in the rectum of a man or a woman; [some people call this [Swahili term]. | NO  YES | 0  1 | **Q1409 and then AND SKIP to SECTION 16** | SEX_EVR |
| Q1402 | How old were you when you had sex for the first time? If you can’t recall the exact age, please give a best estimate. | __ __ YEARS  DON’T KNOW | 88 |  | SEX_AGE |
| Q1403 | How would you describe the first time that you had sex? Would you say that you wanted to have sex, you did not want to have sex but it happened anyway, or were you forced to have sex? | WANTED TO HAVE SEX  DID NOT WANT TO HAVE SEX BUT HAPPENED ANYWAY  WAS FORCED TO HAVE SEX | 1  2  3 |  | SEX_1DES |
| Q1404 | Did you experience any of the following types of situations the first time you had sex?  VERBAL THREATS  PHYSICAL THREATS  PHYSICAL FORCE/HOLDING DOWN  BEATING  HUMILIATING OR DEGRADING SEX ACTS | NO  YES | 0  1 |  | SEX1_VER  SEX1_PHY  SEX1_FRC  SEX1_DEG |
| Q1405 | In total, how many people have you ever had sex with in your lifetime? | __ __ # PERSONS |  | *Note that if this value is less than 3, the participant will only be asked about the corresponding # of partners in the Sexual Network Section | SEXE_NUM |
| Q1406 | In total, how many people have you had sex with in the past 12 months?  This includes people you had sex with only once and people you have had sex with regularly, such as a spouse or someone you live with.  If you can’t recall the exact number, please give a best guess. | NONE  __ __ # PERSONS | 0 |  | SXP12_NUM |
| Q1407 | How many of these partners were women and how many were men? | WOMEN___________  MEN___________ |  | **ASK ONLY IF Q100 = 1**  ***This should total Q1406** | MSM_NUM |
| Q1408 | In general, how would you consider your chances of getting HIV/AIDS? Are they small, moderate, great, or no risk at all? | NO RISK AT ALL  SMALL  MODERATE  GREAT | 1  2  3  4 |  | HIVRISK |
| Q1409 | Have you ever had a test for HIV/AIDS? | NO  YES  DON’T KNOW | 0  1  88 | **Q1501 (UNLESS Q1401 =0)** | TESTHIV |

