**NOTE: This section should only be asked for participants who have had sex (if Q1401=No, Skip this Section)**

*Interviewer:*

**→** I would now like to ask you about your sexual relationships. When I talk about having sex I mean that you had either vaginal or anal sex with the person.

Many people have different types of sexual partnerships. Some sexual partners are people we have sex with once or twice and some sexual partners are people we have sex with regularly. Some people have many sexual partners and other people have fewer sexual partners. Some people have sex with a partner of the same gender.

In the past 12 months, you mentioned that you have had sex with (Response from Q1406) people. I would like to begin by asking you about the person you have had the longest sexual relationship with during the last 12 months.

| **No.** | **Questions and Filters** | | **Coding Categories** | | **Codes** | **Skip to:** | **VARIABLE** |
| --- | --- | --- | --- | --- | --- | --- | --- |
| PARTNER #1 | | | | | | | |
| Q1501 | | Tell me about the person you have had the longest sexual relationship with. What is the nickname or initials I could use to talk about this person? | PARTNER #1 |  | | ASK ENTIRE SECTION ONLY IF Q1401=1 | NAME_P1 |
| Q1502 | | When was the most recent time you had sex with PARTNER 1? | YEARS AGO__ __  MONTHS AGO__ __  WEEKS AGO__ __  DAYS AGO__ __ |  | |  | RECSEX_P1 |
| Q1503 | | Is PARTNER 1 a man or a woman? | MAN  WOMAN | 1  2 | |  | GEND_P1 |
| Q1504 | | Where did you meet PARTNER 1? | HOME  SCHOOL  WORK  MY CAMP  ANOTHER CAMP  MOSQUE/CHURCH  STREET  CLUB/BAR  GUEST HOUSE  BEACH  PARTY  WEDDING/FUNERAL  OTHER___________________ | 1  2  3  4  5  6  7  8  9  10  11  12  13 | |  | MEET_P1  METP1_S |
| Q1505 | | How long have you been having sex with this partner? | YEARS_________________  MONTHS_______________  WEEKS_________________  DAYS__________________ |  | |  | SEXDY_P1  SEXDM_P1  SEXDW_P1 |
| Q1506 | | What type of relationship do you have with PARTNER 1? | SPOUSE  POLYGAMOUS SPOUSE  COHABITING PARTNER  GIRLFRIEND/BOYFRIEND  FRIEND  CASUAL ACQUAINTANCE  COMMERCIAL SEX WORKER  ONE TIME PARTNER  OTHER___________________ | 1  2  3  4  5  6  7  8  9 | |  | RELP_P1  RELP_P1_S |
| Q1507 | | To the best of your knowledge, how old is _____ PARTNER 1? | __ __ YEARS |  | |  | AGE_P1 |
| Q1508 | | Is PARTNER 1 a member of this camp? | NO  YES  DON’T KNOW | 0  1  88 | |  | CAMPM_P1 |

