| Q1509 | | Are you still having sex with PARTNER 1? | NO  YES | 0  1 | |  | SEXCUR_P1 |
| Q1510 | | How often do/did you have sex with PARTNER 1? | EVERY DAY  A FEW TIMES A WEEK  FEW TIMES A MONTH  ABOUT ONCE A MONTH  ONLY 1-2 TIMES EVER | 1  2  3  4  5 | |  | SEXFRQ_P1 |
| Q1511 | | During the last (most recent) time you had sex with this partner, did you use a condom? | NO  YES  DON’T KNOW | 0  1  88 | |  | CNDUSE_P1 |
| Q1512 | | How many times would you say you had sex with PARTNER 1 during the last one month you had sex with him/her? | _____________ |  | |  | NUMSEX_P1 |
| Q1513 | | Of these (Response from Q1512) times, how many times would you say you used a condom? | _____________ |  | |  | NUMCND_P1 |
| Q1514 | | Did you ever give PARTNER 1 money in exchange for having sex with you? | NO  YES | 0  1 | |  | GIVFSP_P1 |
| Q1515 | | Did PARTNER 1 ever give YOU money in exchange for having sex? | NO  YES | 0  1 | |  | RECFSP_P1 |
| Q1516 | | Did you use a condom the last time money was given or exchanged for sex with PARTNER 1? | NO  YES | 0  1 | | **ASK ONLY IF either Q1514 or Q1515 =1** | CNDM_P1 |
| Q1517 | | The last time you had sex with PARTNER 1, did you drink alcohol before or during sex? | NO  YES | 0  1 | |  | DRNK1_P1 |
| Q1518 | | The last time you had sex with PARTNER 1, did PARTNER 1 drink alcohol before or during sex with you? | NO  YES  DON’T KNOW | 0  1  88 | |  | DRINK2_P1 |
| Q1519 | | While you were in a sexual relationship with PARTNER 1, did you have sex with anybody else? | NO  YES | 0  1 | |  | SXCUR_P1 |
| Q1520 | | As far as you know, during the time you were having a sexual relationship with PARTNER 1, do you think PARTNER 1 had sex with other people? | NO  YES | 0  1 | |  | MCP_P1 |
| Q1521 | | How confident are you that you can use a condom with PARTNER 1? | VERY CONFIDENT  SOMEWHAT CONFIDENT  NOT AT ALL CONFIDENT | 1  2  3 | |  | UCND_P1 |
| Q1522 | | How confident are you that you can discuss HIV with PARTNER 1? | VERY CONFIDENT  SOMEWHAT CONFIDENT  NOT AT ALL CONFIDENT | 1  2  3 | |  | TLKHIV_P1 |
| Q1523 | | Have you ever discussed getting an HIV test with PARTNER 1? | NO  YES | 0  1 | |  | TLKTST_P1 |
| Q1524 | | Have you ever gone together with PARTNER 1 for an HIV test? | NO  YES | 0  1 | |  | TOGTST_P1 |
| Q1525 | | Has PARTNER 1 shared the results of their HIV test in the past 12 months? | NO  YES | 0  1 | |  | TSTDISC_P1 |

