| Q1526 | | In the past 12 months, has PARTNER 1 ever hit, slapped, kicked, pushed, shoved or otherwise physically hurt you? | NO  YES | 0  1 | |  | VICVIO_P1 |
| Q1527 | | In the past 12 months, have you ever hit, slapped, kicked, pushed, shoved or otherwise physically hurt PARTNER 1? | NO  YES | 0  1 | |  | PERVIO_P1 |
| PARTNER #2  *Interviewer:*  **→** Now lets talk about your other most recent partners (excluding the partner we just talked about). | | | | | | | |
| Q1528 | | Tell me about the person you had sex with most recently within the last 12 months who is not PARTNER 1. What is the nickname or initials I could use to talk about this person? | PARTNER #2 | |  |  | NAME_P2 |
| Q1529 | | When was the most recent time you had sex with PARTNER 2? | MONTHS __ __  WEEKS __ __  DAYS __ __ | |  |  | RECSEX_P2 |
| Q1530 | | Is PARTNER 2 a man or a woman? | MAN  WOMAN | | 1  2 |  | GEND_P2 |
| Q1531 | | Where did you meet PARTNER 2? | HOME  SCHOOL  WORK  MY CAMP  ANOTHER CAMP  MOSQUE/CHURCH  STREET  CLUB/BAR  GUEST HOUSE  BEACH  PARTY  WEDDING/FUNERAL  OTHER___________________ | | 1  2  3  4  5  6  7  8  9  10  11  12  13 |  | MEET_P2  METP1_S |
| Q1532 | | How long have you been having sex with this partner? | YEARS_________________  MONTHS_______________  WEEKS_________________ | |  |  | SEXDY_P2  SEXDM_P2  SEXDW_P2 |
| Q1533 | | What type of relationship do you have with PARTNER 2? | SPOUSE  POLYGAMOUS SPOUSE  COHABITING PARTNER  GIRLFRIEND/BOYFRIEND  FRIEND  CASUAL ACQUAINTANCE  COMMERCIAL SEX WORKER  ONE TIME PARTNER  OTHER___________________ | | 1  2  3  4  5  6  7  8  9 |  | RELP_P2  RELP_P2_S |
| Q1534 | | (If needed: To the best of your knowledge) How old is _____ PARTNER 2)? | __ __ YEARS | |  |  | AGE_P2 |
| Q1535 | | Is PARTNER 2 a member of this camp? | NO  YES  DON’T KNOW | | 0  1  88 |  | CAMPM_P2 |
| Q1536 | | Are you still having sex with PARTNER 2? | NO  YES | | 0  1 |  | SEXCUR_P2 |
| Q1537 | | How often do/did you have sex with PARTNER 2? | EVERY DAY  A FEW TIMES A WEEK  FEW TIMES A MONTH  ABOUT ONCE A MONTH  ONLY 1-2 TIMES EVER | | 1  2  3  4  5 |  | SEXFRQ_P2 |
| Q1538 | | During the last (most recent) time you had sex with this partner, did you use a condom? | NO  YES  DON’T KNOW | | 0  1  88 |  | CNDUSE_P2 |
| Q1539 | | How many times would you say you had sex with PARTNER 2 during the last one month you had sex with him/her? | _____________ | |  |  | NUMSEX_P2 |

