| Q1540 | | Of these (Response from Q1539) times, how many times would you say you used a condom? | _____________ | |  |  | NUMCND_P2 |
| Q1541 | | Did you ever give PARTNER 2 money in exchange for having sex with you? | NO  YES | | 0  1 |  | GIVFSP_P2 |
| Q1542 | | Did PARTNER 2 ever give YOU money in exchange for having sex? | NO  YES | | 0  1 |  | RECFSP_P2 |
| Q1543 | | Did you use a condom the last time money was given or exchanged for sex with PARTNER 2? | NO  YES | | 0  1 | **ASK ONLY IF either Q1542 or Q1543 =1** | CNDM_P2 |
| Q1544 | | The last time you had sex with PARTNER 2, did you drink alcohol before or during sex | NO  YES | | 0  1 |  | DRNK1_P2 |
| Q1545 | | The last time you had sex with PARTNER 2, did PARTNER 2 drink alcohol before or during sex with you? | NO  YES  DON’T KNOW | | 0  1  88 |  | DRINK2_P2 |
| Q1546 | | While you were in a sexual relationship with PARTNER 2, did you have sex with anybody else? | NO  YES | | 0  1 |  | SXCUR_P2 |
| Q1547 | | As far as you know, during the time you were having a sexual relationship with PARTNER 2, do you think PARTNER 2 had sex with other people? | NO  YES | | 0  1 |  | MCP_P2 |
| Q1548 | | How confident are you that you can use a condom with PARTNER 2? | VERY CONFIDENT  SOMEWHAT CONFIDENT  NOT AT ALL CONFIDENT | | 1  2  3 |  | UCND_P2 |
| Q1549 | | How confident are you that you can discuss HIV with PARTNER 2? | VERY CONFIDENT  SOMEWHAT CONFIDENT  NOT AT ALL CONFIDENT | | 1  2  3 |  | TLKHIV_P2 |
| Q1550 | | Have you ever discussed getting an HIV test with PARTNER 2? | NO  YES | | 0  1 |  | TLKTST_P2 |
| Q1551 | | Have you ever gone together with PARTNER 2 for an HIV test? | NO  YES | | 0  1 |  | TOGTST_P2 |
| Q1552 | | Has PARTNER 2 shared the results of their HIV test in the past 12 months? | NO  YES | | 0  1 |  | TSTDISC_P2 |
| Q1553 | | In the past 12 months, has PARTNER 2 ever hit, slapped, kicked, pushed, shoved or otherwise physically hurt you? | NO  YES | | 0  1 |  | VICVIO_P2 |
| Q1554 | | In the past 12 months, have you ever hit, slapped, kicked, pushed, shoved or otherwise physically hurt PARTNER 2? | NO  YES | | 0  1 |  | PERVIO_P2 |
| PARTNER #3 | | | | | | | |
| Q1555 | | Tell me about another person you had sex with most recently before PARTNER 2. What is the nickname or initials I could use to talk about this person? | PARTNER #3 | |  |  | NAME_P3 |

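### The survey form does not collect condom use as the protocol defines it: window, partners and acts all differ, and some follow-up answers can predate the intervention

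*Protocol*

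**What the plan says.** Section 7.4.1 of the protocol, under consistent condom use, sets the partners as "For each of their three most recent sexual partners" and the measure as "men will report how many times they engaged in sex (oral, anal, vaginal) with these partners during the past month", together with the number of those acts at which a condom was used.

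The Sexual Network paragraph of the same section describes a different group: "up to three partners with whom they have had the longest sexual relationship in the last year".

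Appendix D holds the instrument. Its Section 15 script tells the respondent "When I talk about having sex I mean that you had either vaginal or anal sex with the person". The act counts are asked at Q1512, "How many times would you say you had sex with PARTNER 1 during the last one month you had sex with him/her", and at Q1539, "How many times would you say you had sex with PARTNER 2 during the last one month you had sex with him/her"; Q1566 repeats this for Partner 3. Partner 1 is the longest relationship, placed in the last 12 months by the script. Partner 2 (Q1528) is the most recent other partner within 12 months. Partner 3 (Q1555) is introduced with "Tell me about another person you had sex with most recently before PARTNER 2", with no time limit. A note at Q1405 (lifetime partners) says that if the count is below three, "the participant will only be asked about the corresponding # of partners".

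The behavioural survey paragraph of Section 8.2.3 states that this form serves baseline and both follow-up visits.

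**The concern.** The protocol fixes a definition, and the instrument attached to it collects something else. Consistent condom use and unprotected intercourse are both named secondary endpoints, and Section 9.1.1 quotes detectable odds ratios of 0.74 (sexually active men) and 0.68 (all males) for condom use, although it does not say which condom measure was meant.

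Two things are at stake. First, whoever derives the endpoint must choose a partner set and a window, because the stated one cannot be built from the form. Oral acts were never asked about, and an exact past-month count is not recorded. Second, a month of sex that ended before the intervention cannot respond to it. If such answers enter the follow-up comparison at similar rates in both arms, they pull the estimated difference towards zero.

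**Working it through.** **Side-by-side comparison**

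| Element | Section 7.4.1, condom use | Section 7.4.1, Sexual Network | Appendix D form |
| --- | --- | --- | --- |
| Window | Month before interview | Relationships in the last year | Last month of sex with that partner (Q1512, Q1539, Q1566) |
| Partners | Three most recent | Up to three longest | Longest; most recent other; one before that |
| Acts | Oral, anal, vaginal | Not stated | Vaginal or anal only |

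The windows coincide only when a relationship is current. If last sex was two weeks ago, the form's month runs from roughly two to six weeks before interview, whereas the protocol's month ends at the interview. The partner sets coincide only when the longest partner is also among the three most recent.

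**How far back each partner slot can reach**

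- Partner 1: the script says the last 12 months, but Q1501 does not repeat this and Q1502 accepts an answer in years.
- Partner 2: limited to 12 months by Q1528.
- Partner 3: no stated limit. Q1556 records recency in months, weeks and days.

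**Look-back arithmetic**

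Take month 0 as the start of the intervention (the protocol summary counts 12 and 30 months after intervention). Let V be the visit month and L the months since last sex with the partner. The month asked about runs from V − L − 1 to V − L.

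- Partner within 12 months, L = 12, month-12 visit: 12 − 12 − 1 = −1, so the month runs from −1 to 0.
- Same partner limit, month-30 visit: 30 − 12 − 1 = 17, so the month begins no earlier than month 17.
- Partner with no limit: the month lies wholly before the intervention when V − L ≤ 0. That means L ≥ 12 at the month-12 visit and L ≥ 30 at the month-30 visit. The form allows both.

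Under the window in Section 7.4.1, the visits would cover months 11 to 12 and 29 to 30, both after the start.

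**Size**

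If a share f of counted partnerships predates the intervention, and f and the condom use in those partnerships are the same in both arms, a between-arm difference d becomes d(1 − f). The protocol gives no distribution of time since last sex by partner, so f cannot be estimated.

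**The case against.** Several limits of the form work against a sweeping reading, and most of them stand.

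- A reader might infer that follow-up answers in general can come from any time. They cannot: Partner 2 is limited to 12 months, and the script places Partner 1 there too. Only Partner 3, or a Partner 1 answered in years, is open.
- A reader might infer that month-30 results are as exposed as month-12 results. They are not, as the arithmetic shows.
- A reader might take the Q1405 note to mean that three or more lifetime partners forces three partner loops even when the past year holds one or none. The note only lowers the number when the count is below three; it is a cap, and the script reads back the 12-month count.
- A reader might take the pilot's 47% with two or more partners in the past year (Section 1.7), hence 1 − 0.47 = 53% with fewer, as the share affected. It is not: that base appears to include men who never had sex and skip Section 15, and nothing is said of their earlier partners.
- Dilution assumes old partnerships are equally common in both arms, yet the intervention aims to change partner numbers.

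It can also be argued that Appendix D is the baseline version: its age check uses birth year 1998, and it lacks the moral agency items planned for midpoint and endpoint. But Section 8.2.3 says the form is used at all three visits, so this lowers certainty without removing the problem.

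Finally, recency is already recorded (Q1502, Q1529, Q1556), and a derivation rule could sit in an analysis plan. Such a rule would deal with the timing. It would not recover oral acts or an exact past-month count, and it would leave the protocol's descriptions in conflict.

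**Conclusion.** The contradiction is certain from the text: window, partner set and acts in Section 7.4.1 do not match Appendix D, and the Sexual Network paragraph gives yet another partner set. The form does not collect the stated endpoint.

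The consequence for the treatment comparison is a possibility of unknown size. It rests on two assumptions: that the attached form is the one used at follow-up, and that some men report a Partner 3, or a Partner 1 in years, whose last sex was at least 12 months before the month-12 visit or at least 30 months before the month-30 visit. The likely direction is dilution, but this is a tendency and has not been shown.

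The point concerns secondary endpoints and leaves the two primary endpoints untouched. It should be corrected, since the remedy is cheap.

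**What to change.** Adopt one definition in both paragraphs of Section 7.4.1 and in Appendix D: vaginal or anal acts, one partner set, and one calendar window such as the 30 days before interview. Then take one of two routes.

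1. **Where the form can still change:** reword Q1512, Q1539 and Q1566 to the calendar window, and add a 12-month limit to Q1555.
2. **For data on the existing form:** prespecify that a partner counts only if last sex (Q1502, Q1529, Q1556) falls within a fixed recent window. Use one month, the period in Section 7.4.1, as the main version and 12 months as a sensitivity analysis. With L at most 1, the month asked about begins no earlier than 12 − 1 − 1 = month 10 or 30 − 1 − 1 = month 28. With L at most 12 it can still begin at month −1 at the first follow-up, which is why that version should not be the main one.

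Costs: a smaller denominator, because men without recent sex drop out; and conditioning on sexual activity after randomisation, which the intervention may itself change. To offset the second, also report the outcome among all men, counting a man with no unprotected act in the window as such whether or not he had sex. Rewording items also loses some comparability with baseline answers. The work itself is protocol wording plus four survey items, or a derivation rule alone for data already collected.
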